## Abstract

**Introduction:**

Comprehensive local data on adolescent health are often lacking, particularly in lower resource settings. Furthermore, there are knowledge gaps around which interventions are effective to support healthy behaviours. This study generates health information for students from cities in four middle-income countries to plan, implement and subsequently evaluate a package of interventions to improve health outcomes.

**Methods and analysis:**

We will conduct a cluster randomised controlled trial in schools in Fez, Morocco; Jaipur, India; Saint Catherine Parish, Jamaica; and Sekondi-Takoradi, Ghana. In each city, approximately 30 schools will be randomly selected and assigned to the control or intervention arm. Baseline data collection includes three components. First, a Global School Health Policies and Practices Survey (G-SHPPS) to be completed by principals of all selected schools. Second, a Global School-based Student Health Survey (GSHS) to be administered to a target sample of n=3153 13–17 years old students of randomly selected classes of these schools, including questions on alcohol, tobacco and drug use, diet, hygiene, mental health, physical activity, protective factors, sexual behaviours, violence and injury. Third, a study validating the GSHS physical activity questions against wrist-worn accelerometry in one randomly selected class in each control school (n approximately 300 students per city). Intervention schools will develop a suite of interventions using a participatory approach driven by students and involving parents/guardians, teachers and community stakeholders. Interventions will aim to change existing structures and policies at schools to positively influence students’ behaviour, using the collected data and guided by the framework for *Making Every School a Health Promoting School*. Outcomes will be assessed for differential change after a 2-year follow-up.

**Ethics and dissemination:**

The study was approved by WHO’s Research Ethics Review Committee; by the Jodhpur School of Public Health’s Institutional Review Board for Jaipur, India; by the Noguchi Memorial Institute for Medical Research Institutional Review Board for Sekondi-Takoradi, Ghana; by the Ministry of Health and Wellness’ Advisory Panel on Ethics and Medico-Legal Affairs for St Catherine Parish, Jamaica, and by the Comité d’éthique pour la recherche biomédicale of the Université Mohammed V of Rabat for Fez, Morocco. Findings will be shared through open access publications and conferences.

**Trial registration number:**

NCT04963426.

Strengths and limitations of this studyThis study generates comprehensive individual-level and school-level adolescent health information for direct use to plan, implement and subsequently evaluate a package of interventions to improve health outcomes across four cities from different world regions, with a focus on underserved locations.The approach to develop interventions is data-informed, systematic and evidence-based, culturally adapted and flexible and participatory, driven by adolescents, parents and school and community stakeholders.This study makes use of existing global tools for data collection, intervention planning and implementation and builds on local policies and practices as a foundation for action.The COVID-19 pandemic and related school closures have led to delays in study implementation.Internet connectivity may be poor in some study sites, and alternative methods for study components with electronic data collection may need to be explored.

## Introduction

Adolescence is a unique period in life with rapid physical, cognitive and psychosocial growth. It is an important time for laying foundations of future health, including, for example, establishing behaviours related to non-communicable diseases (NCDs) such as tobacco and alcohol use, diet and physical activity, as well as behaviours linked to sexual or mental health.^1^ Implementing effective, evidence-based interventions could substantially reduce risk behaviours and support protective factors among adolescents and improve their future adult health.^2 3^ However, several critical barriers exist to implementing such interventions for adolescents.

First, there is a lack of relevant and context-specific adolescent health information, particularly in lower resource settings, that is essential to inform intervention planning.^4^ Where data exist, they are primarily national-level estimates on specific health conditions that often mask variations and unequal progress by smaller geographical units.^5 6^ Local data are needed to uncover and address these inequalities and develop the most relevant, effective, age-appropriate and context-specific interventions for adolescents. This includes data on policies and practices affecting adolescent’s behaviour, and on their health behaviours and protective factors. Collecting this information is of particular importance in usually neglected urban settings where little data exist, such as cities other than capitals (called ‘secondary cities’ hereafter).

Second, information on adolescent health is sometimes collected with questionnaires that may not have been validated for the populations in which they are used. Physical activity is one example where the most internationally used questions for adolescents have only been tested for validity in a few high-income countries.^7 8^ To produce useful data to inform decision-making, it is essential for these questions to be tested more widely. Another reason to test adolescent physical activity questions is related to the change in recommended levels of physical activity for this age group. Most currently used questions are based on the 2010 WHO guidelines on physical activity that recommended adolescents to be physically active for at least 60 min *each* day.^9^ In 2020, these guidelines were updated and now state that adolescents should engage in at least *an average* of 60 min of activity per day throughout the week.^10^ Consequently, there is a need for adolescent physical activity questions to be tested against the updated guidelines.

Third, there are significant knowledge gaps about which interventions might be effective in targeting risk behaviours and supporting protective factors in adolescents.^11^ Available evidence is strongest for universal school-based interventions targeting multiple risk behaviours, however, most of the included studies were conducted in high-income countries, while evidence from lower resource settings is lacking.^11^

Fourth, adolescents are too rarely involved in health promotion planning, decision-making and implementation. Yet, participatory approaches engaging adolescents are crucial for sustainable change in cognitions and behaviour^12 13^ and thus warranted.

Global tools that help overcome the aforementioned barriers exist. The Global School Health Policies and Practices Survey (G-SHPPS) generates important school-level policy information.^14^ The Global School-based Student Health Survey (GSHS) collects data on students’ health behaviours and protective factors.^15^ The Global Accelerated Action for the Health of Adolescents (Global AA-HA!) provides a systematic, participatory approach to understanding adolescent health needs based on data, prioritising these needs in the local context and planning, implementing, monitoring and evaluating appropriate interventions.^16^ The initiative *Making Every School a Health Promoting School* provides an evidence-based framework for the implementation of eight Global Standards to improve students’ health^17^ and promotes a whole-school approach that has demonstrated positive effects on health.^18–21^ Both the Global AA-HA! and *Making Every School a Health Promoting School* emphasise the importance of students’ involvement in health promotion planning, decision-making and implementation in a manner that is empowering. Finally, photovoice facilitates adolescent engagement by allowing them to pictorially take impressions of health facilitators and barriers in their schools and community to inform intervention planning.^22–24^

These available global tools will be used to achieve the goals of this study. The overarching aim is to generate health information for students of secondary cities from four middle-income countries of different world regions that will be directly used to plan, implement and evaluate a package of interventions for programme planning, policy and structural change to improve students’ health.

Specific objectives include: First, to assess current health policies and practices in selected schools of the four cities. Second, to understand the levels of health risk and protective factors among school-going adolescents in these cities. Third, to validate currently used questions to assess students’ physical activity behaviour with wearable accelerometers. Fourth, to plan and evaluate a participatory intervention approach that focuses on changing existing structures, policies and practices and on implementing programmes in and around schools to improve health outcomes for students.

## Methods and analysis

### Study design and locations

We will conduct a multisite two-armed cluster randomised controlled trial using a nested cross-sectional design. The clusters are defined as schools and classes within schools. The study locations are spread across four world regions and include the cities of Fez, Morocco; Jaipur, India; Saint Catherine Parish, Jamaica; and Sekondi-Takoradi, Ghana. These locations (secondary cities) were purposefully selected in collaboration with WHO regional focal points to generate information for settings that are less likely to be in the focus or receive resources for adolescent health interventions.

In each city, approximately 30 schools will be selected and randomly assigned to either the intervention or control group. At baseline, all sampled schools will conduct a G-SHPPS to assess school policies and practices^14^ and a GSHS to assess risk behaviours and protective factors among students.^15^ Additionally, in the control group of each city, we will conduct studies to validate GSHS physical activity questions against an accelerometer (Axivity AX3^25^) to be worn by students on the wrist for 8 days prior to the baseline survey.

Following the baseline surveys, the intervention schools will participate in data-to-action workshops to develop a package of interventions. Students, parents, teachers, local authorities and researchers will work together to find and prioritise policy and programme solutions to establish a unified action plan. Subsequently, these interventions will be implemented, and study processes and outcomes will be assessed for differential change via repeat G-SHPPS and GSHS surveys after a 2-year follow-up. At follow-up, new classes will be selected from the same schools to ensure participation of 13–17 years old students similar in age to the baseline sample. We hypothesise that the prevalence of behavioural risk factors would be lower and the prevalence of protective factors higher among students in schools in the intervention group compared with the control group at follow-up. An overview of our study design is shown in figure 1.

**Figure 1 F1:**
[figure not shown]
Overview of the study design. ^a^ GSHS, Global School-based Student Health Survey; ^b^ G-SHPPS, Global School Health Policies and Practices Survey.

### Study population and sampling

This study’s target population is 13–17 years old students. In each city, following standard G-SHPPS and GSHS sampling procedures,^14 15^ approximately 30 schools will be randomly selected from a list of schools including every school in the city with eligible classes (classes that the target population usually attends), provided by education authorities from the respective cities. Selection will be done by experts from WHO with probability proportional to the number of students in the eligible schools.

For the GSHS, in a second sampling stage, classes will be randomly selected from all eligible classes. All students of selected classes will be asked to participate in the survey.

The city sample size was calculated to test the hypothesis that the prevalence of behavioural risk factors would be lower among students in the schools of the intervention group versus those in the control group at follow-up using G*Power V.3.1.^26^ With most outcome variables (prevalence of behavioural risk and protective factors) being binary, logistic regression was selected as the statistical test, the required power level was set at 80% and the significance level prespecified at α=0.05. The to-be-detected effect was specified at an OR=0.75, which represents the average of pooled effect sizes from a recent meta-analysis^11^ considering universal school interventions across a range of behaviours, similar to the ones assessed in our study.

The initial sample size calculation resulted in n=473, which was inflated assuming a design effect of 1.5 and an expected response rate of 90%: 473×1.5/0.9=788. Finally, this sample size was quadrupled aiming at reporting for two age groups within both the intervention and control arm: 13–15 and 16–17 years, resulting in a target sample size of n=3153.

Participation in the G-SHPPS and GSHS is voluntary. For the GSHS, in line with local policies, consent will be obtained from the students themselves and/or their parents/guardians (see online supplemental appendix for consent forms).

10.1136/bmjopen-2022-071353.supp1Supplementary data

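### The base sample size of 473 does not give 80% power for a two-arm contrast at OR 0.75; the delivered city sample nearly does for common outcomes, but not for less common ones

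*Protocol article*

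**What the plan says.** In Study population and sampling, the article states that the city sample size was calculated in G*Power 3.1 for the hypothesis that behavioural risk factors "would be lower among students in the schools of the intervention group versus those in the control group at follow-up". The ingredients are:

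- Test: "logistic regression was selected as the statistical test".
- Error rates: 80% power and "the significance level prespecified at α=0.05".
- Effect: "The to-be-detected effect was specified at an OR=0.75", described as an average of pooled effects of universal school interventions.
- Result: "The initial sample size calculation resulted in n=473".

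The 473 is then inflated for a design effect of 1.5 and a 90% response rate to 788, and multiplied by four so that results can be reported for two age groups in each arm. This gives the 3153 that the Abstract repeats ("to be administered to a target sample of n=3153"). The article does not print the assumed prevalence, the distribution chosen for the predictor, the sidedness or the allocation ratio.

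**The concern.** The predictor under test is trial arm, which takes two values. An OR of 0.75 between two arms is a modest effect, and 473 students in total is far fewer than a two-group comparison of that size normally needs. If the base figure is wrong, 80% power was not established at the step where it is claimed, and 788 and 3153 are built on a number that does not mean what the text says.

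What is at stake is how the follow-up results are read. A reader who trusts 80% power for every binary outcome in every city could take a null result on an uncommon behaviour as evidence of no effect, when the comparison had much less chance of detecting an OR of 0.75.

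**Working it through.** **Inputs.** From Study population and sampling: OR 0.75, power 80%, α 0.05, design effect 1.5, response 90%, multiplier 4. Assumed because not printed: 1:1 allocation; a two-sided test as base case, with one-sided also shown; control prevalence p0 varied.

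**Formula.** Wald sample size for a logistic coefficient: N = (z_α + z_β)² × V / (ln OR)², where V/N is the variance of the estimated log OR. Here (1.960 + 0.842)² = 7.849 two-sided, (1.645 + 0.842)² = 6.183 one-sided, and (ln 0.75)² = 0.08276.

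**Step 1: reproduce 473.** With a standard-normal predictor and base rate 0.30, the information matrix gives V = 4.981, so N = 7.849 × 4.981 / 0.08276 = 472.4, rounded up to 473. A base rate of 0.70 gives the same. The later chain also reproduces: 473 × 1.5 / 0.9 = 788.3, and × 4 = 3153.3.

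**Step 2: use a binary arm.** For a 50:50 indicator, V = 1/(0.5 p0 q0) + 1/(0.5 p1 q1), with p1 following from p0 and OR 0.75. At p0 = 0.30, p1 = 0.243 and V = 20.389, about four times the value in step 1, as expected when the predictor variance is 0.25 instead of 1.

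- Two-sided total N: 4,779 at 10%, 2,612 at 20%, 1,934 at 30%, 1,533 at 50%. The minimum is 1,525, near 53.6%.
- One-sided minimum: 6.183 × 16.083 / 0.08276 ≈ 1,201.
- Pooled two-proportion and variance-corrected versions put the two-sided minimum at 1,520 to 1,522 and the one-sided minimum at about 1,198. None comes near 473.

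**Step 3: power of 473.** Power ≈ Φ(|ln OR| / √(V/N) − z_α). With 473 in total, two-sided power is 28% at 30% prevalence and at most 34.5% at any prevalence; one-sided it is at most 47%. Read as 473 per arm (946 in total), it is at most 60% two-sided and 71% one-sided.

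**Step 4: what the target of 3153 delivers.** Removing non-response and the design effect: 3153 × 0.9 / 1.5 ≈ 1,892 effective students per city, and half of that, about 946, in one age group. Example at 30%: √(20.389/1,892) = 0.1038; 0.2877/0.1038 = 2.771; Φ(2.771 − 1.960) = 79%.

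| Control prevalence | 50% | 30% | 20% | 10% |
|---|---|---|---|---|
| Whole city, power at OR 0.75, two-sided | 88% | 79% | 66% | 42% |
| Whole city, power at OR 0.75, one-sided | 93% | 87% | 77% | 55% |
| One age group, power at OR 0.75, two-sided | 60% | 50% | 39% | 24% |
| Whole city, OR detectable with 80% power, two-sided | 0.77 | 0.75 | 0.71 | 0.62 |
| One age group, OR detectable with 80% power, two-sided | 0.69 | 0.66 | 0.61 | 0.48 |

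Two-sided whole-city power reaches 80% from about 31% prevalence to just under 75%. One-sided, it falls below 80% at about 22% prevalence.

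**The case against.** The strongest reply is that nobody will analyse 473 students. The target is 3153, the hypothesis that was sized is the whole-city contrast, and the fourfold multiplier almost exactly cancels the fourfold variance gap. This stands: a reader who saw only the 28% to 35% figures might infer that the trial is grossly underpowered, and the article does not support that. For outcomes in the middle of the prevalence range the city comparison is close to or above 80%. But the cancellation is a coincidence. The text gives a different reason for the multiplier, and the offset does not reach 80% two-sided below about 31% prevalence.

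A reader might also infer that the authors entered trial arm as a normally distributed covariate. The match to 473 is exact, but it was found by searching over settings that are not printed, and other continuous-predictor settings come within a student or two (474, for example, by another formula at 50% prevalence with R² of 0.2). The cause is probable, not documented. The shortfall does not depend on it.

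A third tempting reading is that the protocol promises powered tests within age groups. It does not: it speaks of reporting by age group, which fits prevalence estimates with confidence intervals, and no age-specific effect test is described. What remains is that scaling a powered n by the number of cells can leave the impression that each age group is powered.

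Finally, the hypothesis is directional and sidedness is not stated. A one-sided test improves the delivered figures but does not rescue 473.

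**Conclusion.** The point holds. As printed, 473 is incompatible with the stated test, effect, α and power. This is a wrong figure, not a detail left to an analysis plan. A 1:1 binary arm needs at least 1,525 in total two-sided, or about 1,200 one-sided, which is 2.5 to 3.2 times as many.

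The practical consequence is narrower than that ratio suggests. At the target of 3153 the whole-city contrast has roughly the claimed power for common outcomes and too little for less common ones, down to 42% two-sided at 10% prevalence. Arm contrasts within an age group have at most 60%. The article gives no prevalences, so how many of the outcome indicators are affected cannot be said.

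These figures assume 1:1 allocation, an effect of OR 0.75, full recruitment to target, and the article's own design effect of 1.5. That last assumption matters: if the design effect were 2 (illustrative only), 3153 × 0.9 / 2 ≈ 1,419 effective students would give 67% two-sided at 30% prevalence instead of 79%.

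**What to change.** Recompute the base sample size with a binary 50:50 predictor, and state the sidedness and the assumed control prevalence. Keep the target of 3153 and replace the single 80% statement with a short table of delivered power and detectable OR by control prevalence for the whole-city contrast, noting that it depends on the design effect of 1.5. Add one sentence saying that the sample size does not power arm contrasts within age groups.

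The cost is a short recalculation and a change of wording, best made before the follow-up data are analysed. No extra students are needed and the described analysis need not change. The stated power becomes less favourable for less common outcomes.

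### The n=473 behind the stated 80% power cannot be a two-arm sample size at OR 0.75, and no power is given for the n=3153 actually targeted

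*Protocol article*

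**What the plan says.** All of this is in the Protocol article, Study population and sampling.

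- Purpose: "The city sample size was calculated to test the hypothesis that the prevalence of behavioural risk factors would be lower among students" in intervention schools than in control schools at follow-up.
- Test and error rates: "logistic regression was selected as the statistical test", "the required power level was set at 80" per cent, and "the significance level prespecified at α=0.05".
- Effect: "The to-be-detected effect was specified at an OR=0.75".
- Result: "The initial sample size calculation resulted in n=473". A design effect of 1.5 and a 90% response rate take this to 788.
- Final step: "this sample size was quadrupled aiming at reporting for two age groups within both the intervention and control arm", which gives 3153.

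The section does not give the control prevalence, the distribution assumed for the predictor, whether the test is one- or two-sided, or whether 473 is a total or a per-arm figure. It states no power for 3153, either for the whole city or by age group.

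**The concern.** The hypothesis that was sized compares two arms, so the predictor of interest is a 0/1 indicator. For an odds ratio as close to 1 as 0.75, 473 students is far too few for such a comparison. The final step then multiplies by four for age group and arm, not for a power target, so 80% cannot simply be carried forward to 3153.

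The 80% is the article's only power figure. Readers will apply it to the trial as run, and perhaps to the age groups for which the sample was enlarged. If the real power is much lower for low-prevalence indicators or within an age group, a non-significant result there could be misread as evidence of no effect.

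**Working it through.** **1. The plan's own chain.** 473 × 1.5 / 0.9 = 788.3, and 788.3 × 4 = 3153.3. The arithmetic reproduces.

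**2. What a two-arm contrast needs.** From the plan: OR 0.75, α = 0.05, power 80%. Assumed: 1:1 allocation, two-sided test, control prevalence p varied. With intervention prevalence q = 0.75·odds(p) / (1 + 0.75·odds(p)), the Wald sample size for the log odds ratio is

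N(total) = 2 × (1.960 + 0.842)² × V / (ln 0.75)², where V = 1/[p(1−p)] + 1/[q(1−q)],

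with (1.960 + 0.842)² = 7.849 and (ln 0.75)² = 0.08276.

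| p | q | V | N total |
|---|---|---|---|
| 10% | 7.7% | 25.19 | 4,779 |
| 20% | 15.8% | 13.77 | 2,612 |
| 30% | 24.3% | 10.19 | 1,934 |
| 50% | 42.9% | 8.08 | 1,533 |

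The minimum over all prevalences is about 1,525 in total (about 763 per arm), at p near 54%. One-sided, it is about 1,201 in total (about 601 per arm). Both per-arm minima exceed 473, so 473 is neither the total nor the per-arm size.

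**3. Power at 473.** Power = Φ(|ln 0.75| / √(V/n per arm) − 1.960). With 473 as the two-arm total it is 14%, 22%, 28% and 34% at p = 10%, 20%, 30% and 50%, and it peaks at about 34%. With 473 per arm (946 in total) it peaks at about 60%.

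**4. Where 473 may come from.** This is inference, since the article does not give the inputs. For a standard normal predictor with OR 0.75 per standard deviation, event probability 0.30 and a two-sided test, the Wald logistic formula gives 7.849 × 4.981 / 0.08276 = 472.4, which rounds up to 473. The 4.981 is the slope variance per observation. A balanced 0/1 arm indicator has variance 0.25 against 1 for that predictor, so the two-arm requirement is about 4 × 473 = 1,892, close to the 1,934 in step 2.

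**5. Power at 3153.** Effective n = 3153 × 0.9 / 1.5 = 1,892 for the city, and 946 per age group if the two groups are equal.

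| Control prevalence | Whole city (1,892) | One age group (946) |
|---|---|---|
| 10% | 42% | 24% |
| 20% | 66% | 39% |
| 30% | 79% | 50% |
| 50% | 88% | 60% |

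The age-group column peaks at about 60%. One-sided, it peaks at about 71%, still below 80%.

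**The case against.** Three points can be made for the plan.

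- **The final sample may be adequate for the main contrast.** This stands in part. At 30% control prevalence the whole-city contrast has about 79% power, and more at 40% to 50%. The fourfold step roughly offsets the shortfall in 473. But the article neither derives nor states this, and it fails at lower prevalence.
- **The article speaks of reporting by age group, not of testing.** This also stands. Four arm-by-age cells are a coherent basis for reporting prevalence with confidence intervals, and nowhere is 80% power promised within an age group. It does not explain how 473 yields 80% power for the two-arm hypothesis.
- **An article may leave inputs to the full protocol.** That excuses the unstated prevalence. It does not excuse a printed n that no control prevalence can reconcile with the printed odds ratio, power and α under 1:1 allocation.

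A reader might also infer that 473 already includes both arms, so that two age groups need a factor of two and the sample is twice what is required. The document does not support this. It never says that 473 is a two-arm total, and step 2 shows that it cannot be an adequate one. Doubling 788 would give 946 effective students for the whole city, with at most about 60% power. Nor can it be said that 80% is wrong for every comparison: the whole-city contrast comes close at about 30% prevalence.

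**Conclusion.** The concern holds for the derivation and the power statement. The 473 does not give 80% power for the hypothesis it is attached to, and the factor of four does not come from a power target. At n=3153, whole-city power runs from about 42% to 88% over control prevalence 10% to 50%, and age-group power from about 24% to 60%. The documents do not show that the sample is too large.

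These figures assume 1:1 allocation, a two-sided test, an equal age split, and the plan's design effect of 1.5 and 90% response. The design effect matters. With about 30 schools, a larger sample means more students per school. If 1.5 was chosen for 788 invited (788.3 × 0.9 / 30 = 23.6 responders per school), the implied intracluster correlation is 0.5 / 22.65 = 0.022. At 3153 invited (94.6 per school) the design effect would be 1 + 93.6 × 0.022 = about 3.1, leaving about 926 effective students and roughly 50% whole-city power at 30% prevalence. If 1.5 was meant for 3153, the power table stands as shown.

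**What to change.** Redo the calculation with arm as a binary predictor. State the control prevalence, allocation ratio and sidedness, whether n is total or per arm, and the cluster size to which the design effect of 1.5 applies. Replace the 80% attached to 473 with the power that n=3153 gives for (a) the whole-city arm contrast and (b) each age-group contrast, over a range such as 10% to 50% control prevalence. Name (a) as the powered analysis and label age-group effects descriptive. The text should not say that the multiplier ought to be two or that the sample is oversized.

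The cost is a short recalculation and a few rewritten sentences, with no change to recruitment. The price is a less favourable power statement for low-prevalence indicators and for the age groups.
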